## Trial management and monitoring

### Data management

All data management will be undertaken by the University of Granada (UGR) (Spain) and Odense University Hospital (Denmark). In Spain, standard operating procedures will be in place for the collection and handling of data. All study data will be entered directly by trained and delegated research staff included in the STOP project into a secure, bespoke electronic trial database with inbuilt range checks set up and hosted by the University of Granada. User accounts will be allocated and managed centrally by the trial coordinator and restricted to appropriate site level access. Data collected on the forms and entered into the electronic database will only identify the participants by a unique trial number. No identifiable data will be stored in the trial database.

In Denmark, study data are collected by trained project midwives from the STOP project following a manual for data collection and will be entered directly to a secure web-based database designed to support data capture for research studies with inbuilt range checks (REDCap) (project-redcap.org). User access to the database is restricted and assigned by the Danish trial coordinator. Data is entered into the database with a unique study trial number, and there will be no identifiable data in the database. Data with invalid study trial numbers, values outside the range or follow-up id that do not match the baseline study trial number, will be excluded.

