### Eligibility criteria

All women who fulfil the inclusion criteria will be screened and invited to receive an e-health package. Of those who accept the e-health intervention, 20 women will be randomised, 10 women in each country. In Spain and Denmark, respectively, 5 will be allocated in the intervention group and 5 will be asked to consent to be in the control group.

Inclusion criteria: pregnant women at <12 weeks gestation, who screen positive in IPV at the first antenatal visit and accept the e-health package.

Exclusion criteria: (1) women who cannot be informed about the study without their partners or other family members knowing; (2) mentally or physically incapacity to participate in the study; (3) women below 16 years in Spain or below 18 years in Denmark; (4) inability to understand Danish/Spanish, (5) lack of internet and electronic device and (6) women with extreme severity of IPV. Women selected to participate in the trial in this situation will receive an evaluation of danger before randomisation. If the severity of IPV is confirmed to be at high level of danger, these pregnant women will be routinely treated and supported according to the standard protocol in each country. Following this path, any potential risk for the women will be taken into account from the beginning of the process and women will be protected. Women who have same-sex partners will be screened, but their data will not be used for the purpose of this study.

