Qualitative data will be collected through individual in-depth interviews with a few women at any point of the flow diagram (Fig 2) to explore their opinion and experiences of the study procedures and intervention. Additionally, we will conduct interviews with the IPV counsellors (midwives in Denmark and psychologist and midwives in Spain) to explore their experiences with the delivery of the intervention and their opinion about a future full-randomised controlled trial. A semi-structured interview guide will be developed for the interviews using the Model for Assessment of Telemedicine Applications (MAST) as theoretical framework [38] with focus primarily on the following domains: users’ perspectives, their safety, ethical and organisational aspects; health problems and technology. All participants will give written consent prior to the interviews starting and data collection will stop once data is saturated. The interviews will be conducted in Danish/Spanish and audio recorded, and will be transcribed and analysed by use of a thematic content analysis using a combined inductive-deductive approach [39]. A coding frame will be developed, and themes will deductively be derived from MAST and supplemented with categories that inductively arise from the data. See Fig 1 for an overview of intervention and assessments.

Data will be collected by trained health personal and researchers in the STOP (Stop Intimate Partner Violence in Pregnancy, https://stop-ipv.eu) Project. On reasonable request, protocol, data collection forms and plans for statistical analysis will be available from investigators. In case of failure to provide data in the follow-up assessments, we will follow the above described STOP protocol for follow up. In Spain, the participant will be contacted by the preferred mean: phone or email. If a woman indicates she wants to be contacted by phone, the psychologist will make a maximum of three phone calls at different times and days. If the contact is made by email or phone message, the counsellor will send a maximum of two attempts leaving between both at least three days. In Denmark, women in the project will indicate if they prefer to be contacted by phone or email at the inclusion. If an included woman is unreachable, a project midwife will try to establish contact at 3 different occasions within 6 weeks. Rate of failure to obtain data will be one of the outcome measures.

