#### Progression criteria

Table 1 outlines the main criteria that will be considered to assess the feasibility of a full-scale RCT. In addition, our qualitative findings will also be used to support the decision-making around progression to a full-scale trial. For example, if a progression criterion outlined in Table 1 does not meet the threshold for progression, but we have developed a qualitative understanding of why this occurred and how it could be improved, then it may still be possible to proceed with the full trial. The research team of the STOP project will have access to these interim results.

**Table 1 pone.0282997.t001:** Suggested progression criteria in eIPV trial.

Feasibility objectives and related data to be collected	Go criteria to proceed to full trial	Criteria to reassess and adjust full trial protocol	Stop criteria
Study population			
1. Consent rate of eligible women	Rate >25% of eligible women agreeing to participate.	Rate between 11% and 24% women agreeing to participate	Rate <10% of eligible women agreeing to participate
Study outcomes			
2. Proportion of women in either intervention or control group for whom the allocated treatment is adhered to.	Adherence to allocated treatment in >80% of study sample.	Adherence to allocated treatment in between 51% and 79% of study sample.	Adherence to allocated treatment in <50% of study sample.
RCT process			
3. Collection of data on clinical outcomes	Complete data available of >80% of study sample.	Missing data between 21% and 49% of study sample.	Data missing of >50% of study sample.

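### The Danish rule excludes invalid or mismatched data with no query step first, so clerical errors can be counted as missing data and lower the completeness rate

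*Protocol article*

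**What the plan says.** For Denmark, the Data management section of the protocol article lists three kinds of faulty data (an invalid trial number, an out-of-range value, a follow-up identifier with no matching baseline identifier) and gives one disposition for all of them: "values outside the range or follow-up id that do not match the baseline study trial number, will be excluded". No query, source check or correction comes before it. The same section says that trained project midwives collect the Danish data following a manual, and that the database has range checks built in.

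For Spain it says "In Spain, standard operating procedures will be in place for the collection and handling of data" and also mentions range checks, but it prints no exclusion rule.

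Completeness of outcome data is used in three places:
- It is a secondary outcome, reported as a rate in each arm.
- The section on study interventions and assessments says "Rate of failure to obtain data will be one of the outcome measures".
- Criterion 3 of Table 1 (Progression criteria) sets Go at "Complete data available of >80% of study sample".

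The sample is small: "20 women will be randomised, 10 women in each country", five per arm within each country.

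The Confidentiality section says that the research team can link the baseline and outcome databases through the woman's date of birth and telephone number.

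**The concern.** The pilot is meant to learn whether outcome data can be obtained from these women. A mistyped identifier or an implausible entry is a fault of data handling and says nothing about whether the woman responded. Under the rule as printed, the two become one number: data that were obtained and then discarded look the same as data never given.

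The distortion runs in one direction, since exclusion can only lower completeness. It is also avoidable. With ten Danish women, a faulty entry can be traced to its source, and the protocol itself describes a second way of linking the databases. Built-in range checks help with out-of-range values. They do not help with a follow-up identifier that is in range but matches no baseline record.

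At stake are the reported completeness rates, which will be used to plan follow-up in the full trial, and to a lesser degree the reading of criterion 3.

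**Working it through.** The plan has no derived figure to reproduce here. The Go threshold is a fixed number, and no power calculation is given. The check asks how much the rule could move completeness, and the chance of Go, across a range of assumptions.

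**Inputs from the protocol.** 20 women randomised, 10 of them Danish (Eligibility criteria); Go if more than 80% of the study sample has complete data (Table 1).

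**Inputs assumed, because the protocol gives neither.** True completeness before any exclusion, c: 85% to 100%. Share of Danish women who become incomplete through the rule, e: 0% to 10%, with larger values where stated. Women are treated as independent, and the rule is applied to Danish women only.

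**Step 1: how many exclusions lose Go.** With otherwise complete data and k women lost, completeness is (20 − k)/20.
- k = 1, 2, 3: 95%, 90%, 85%. All are still Go.
- k = 4: 16/20 = 80%, which is not above 80%, so Go is lost. This result also lies outside the middle band, "Missing data between 21% and 49% of study sample", because 20% are missing.

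Go therefore needs at least 17 of 20, and exclusions alone must remove 4 of the 10 Danish women to lose it. In one arm of 10, or among the 10 Danish women, each exclusion costs 10 percentage points.

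**Step 2: chance that exclusions alone lose Go (c = 100%).** P(Binomial(10, e) ≥ 4) is about 0.001 at e = 5%, 0.013 at 10%, 0.121 at 20% and 0.350 at 30%.

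**Step 3: bias in the rate.** Expected Danish completeness is c(1 − e), so the Danish bias is c × e. In the whole sample it is half of that, because half the women are Danish. With c = 90%:
- e = 5%: 0.90 × 0.05 = 4.5 points in Denmark, 2.25 points overall.
- e = 10%: 0.90 × 0.10 = 9 points in Denmark, 4.5 points overall.

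**Step 4: chance of Go when some data are also missing for other reasons.** The number complete is Binomial(10, c) for Spain plus Binomial(10, c(1 − e)) for Denmark, and P(Go) = P(total ≥ 17).

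| True completeness c | e = 0 | e = 2% | e = 5% | e = 10% |
|---|---|---|---|---|
| 100% | 1.000 | 1.000 | 0.999 | 0.987 |
| 95% | 0.984 | 0.972 | 0.945 | 0.879 |
| 90% | 0.867 | 0.833 | 0.777 | 0.672 |
| 85% | 0.648 | 0.606 | 0.544 | 0.444 |

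The e = 0 column is what applies if every such error is queried and corrected. The loss attributable to the rule is the difference along a row. At c = 90% it is 0.867 − 0.777 = 0.090 for e = 5% and 0.867 − 0.672 = 0.195 for e = 10%. At c = 95% it is 0.039 and 0.105.

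**The case against.** A reader might infer that the rule will push completeness below the Go threshold. The documents do not support that. They give no error rate, and Step 1 shows that four women must be lost when data are otherwise complete. Trained staff, a manual and range checks should keep such errors few. The larger drops in Step 4 appear only when other data are already missing, and at 90% true completeness a chance of 1 − 0.867 = 0.133 of missing Go exists without any exclusion.

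A reader might also infer that whole records are dropped. The sentence speaks of data, which may mean only the offending value. Whether one missing value makes a woman incomplete depends on a definition of complete that the article does not give. So e must be read as the share of women made incomplete, not as a share of entries.

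A third inference is a proven bias between the countries. Spanish handling rests on operating procedures that are not shown. The absence of a printed rule does not establish that Spain handles such data differently.

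The threshold is also not binding: the Progression criteria section allows the full trial to proceed after a missed criterion if the reason is understood and could be improved. A wrong decision is therefore less likely. This does not repair the reported rate, and the reason is visible only if clerical exclusions are counted separately.

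Finally, queries are often described in a manual, and the sentence may refer to data that remain invalid after them. It does not say so. The article states a disposition, and that disposition is exclusion. A follow-up identifier that wrongly matches another woman's baseline number escapes the rule altogether, so the point concerns only invalid or unmatched identifiers and out-of-range values.

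**Conclusion.** The point holds in a limited form. As printed, the Danish rule can turn data a woman supplied into missing data. That lowers Danish completeness, blurs the outcome on failure to obtain data, and could contribute to missing the Go criterion.

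The size depends wholly on assumed rates. If 5% to 10% of Danish women were affected, the overall completeness rate would fall by about 2 to 5 points at 90% true completeness. The chance of Go would fall by 0.09 to 0.20 at 90% true completeness and by 0.04 to 0.11 at 95%. With otherwise complete data the chance of losing Go stays near 0.01 or below. That the threshold will be missed, or that the two countries are treated differently, is not established. The pilot is not invalidated, but the sentence is worth correcting because the remedy costs almost nothing.

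**What to change.** Replace the Danish exclusion sentence with a rule along these lines:
- Out-of-range values and invalid or unmatched identifiers are first queried against the source and corrected. The link by date of birth and telephone number described under Confidentiality may be used for identifiers.
- Only a value that cannot be resolved is set to missing; the rest of the woman's data are kept.
- The same rule is confirmed for both countries.
- Unresolved clerical exclusions are reported by country and arm, separately from women who gave no data.

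The cost is one revised paragraph and a few queries in a study of 20 women.

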### Trial management

The trial is managed and run by the University of Granada and Odense University Hospital. Both centers are responsible for safety reporting, coordination of trial committees, statistical analysis and reporting, trial monitoring, database management and case report form design.

### Pilot trial oversight

An advisory board has been established to oversee and monitor the trial conduct and patient safety. It is chaired by an independent professor from Norway ([name]), with two other independent IPV experts from Spain and Denmark ([name] and [name] [name]). The advisory board provides overall supervision of the trial and ensures that it is being conducted according to the protocol, good clinical practice and relevant regulations. The advisory board also monitor trial progress in relation to recruitment, data capture and completeness, protocol adherence and deviations and subject withdrawals. The board will meet at the request of the investigators. It will be responsible for reviewing the trial data and assessing whether there are any safety issues that need to be brought to the attention of the sponsor, or any ethical reasons why the trial should not continue. Given the low risk of the study intervention and that it is non-blinded, no separate data safety monitoring committee will be established. The sponsor retains the right to audit the study, including any study site or central facility.

### Protecting participants and safety reporting

By taking part in the study, participants will automatically enter a project where a greater level of care will become available to them. The study has well-established security protocols. The screening questionnaires will capture the severity of violence permitting us to refer women at high risk of danger to the relevant national authorities responsible their protection. During of the first videocounselling session, even if the questionnaires did not register a high level of risk, the danger to the life of the participants will be specifically evaluated. If a risk of danger is detected, the same protocol as above will be applied. All the videocounselling sessions will be carried out with a high level of vigilance concerning danger. It should be noted that the intervention itself (as explain above) contains features that are protective, for example, a link that expiries after the counseling sessions, a protection plan back by easy-to-use features to activate emergency contacts, camouflage of the app and emergency exit button. The videocounselling providers will receive in-session protection training, for example, to change the topic of the conversation in case the partner shows up unexpectedly during the sessions. Videoconsellors and women will talk about these options at the beginning of the intervention; in this way both will know what to do if something like this happens.

For safety reporting, if severe or life-threatening abuse of a pregnant woman is identified by the IPV counsellors, the principal investigator will be notified and the woman will be treated according to the standard protocol in each country. The study does not add any risk or harm for the women, we will therefore not provide a post-trial care for compensation. On the contrary, it is anticipated that video counselling addressing safety behavior and safety planning has the potential to increase safe behaviors and thus decrease IPV exposure. We also anticipate that the participating midwives will experience a greater competence and confidence in approaching the topic of violence and handling women who are exposed to IPV. Women will benefit from health professionals who enquire in an appropriate way about violence. In addition, information will be provided about IPV community resources which the women may make use of after the e-health intervention is finished.

#### Patient and public involvement

Two women previously exposed to IPV (one Spanish and one Danish) form the target group representatives. They will help develop a more pregnant women-centred information sheet in line with the well-known need to involve citizens in science [43]. The qualitative research embedded within this pilot study will prove integral in evaluating how the consent materials and processes were received in practice.

## Discussion

Even though numerous intervention models to address IPV have been developed, current efforts suffer from limitations. First, IPV services are often not integrated within routine health service delivery, and second, models for integrating IPV service in health service delivery where developed tend not to have generalizability to the European context [14–20]. To address the personally and politically sensitive problems associated with IPV among pregnant women, effective, sustainable, and culturally appropriate health system-based interventions need development. If found effective, e-health interventions would be suitable for incorporation in these care pathways.

Screening for IPV combined with an empowerment intervention that includes education and video counselling on safety planning may have potential to address repeated IPV and associated adverse health effect among pregnant women. The option of receiving counselling and support through video consultation during antenatal care presents an opportunity for more accessible and flexible care addressing some of the barriers associated with in-person care, such as travel distance and time, travel costs, and the stigma of seeking help. In addition, patients may be more motivated to seek and continue treatment if they are in a familiar environment of their own choice and can avoid stressful situations, such as navigating a hospital or maternity facility. The development of the video counselling intervention will capture the need for safety and adhere to strict security features preventing the risk of women’s partners prying on their online activity. These provisos need underpinning effectiveness evidence.

Prior to performing a large interventional trial, a pilot study is needed to identify barriers to recruitment, assess feasibility and acceptability of the treatment, and fine-tune study procedures. No RCT has previously assessed an e-health intervention in IPV among pregnant women in comparison with a control group (with a delay intervention). In this pilot trial, we chose to perform randomisation with a modified Zelen’s design rather than simple randomisation for several reasons. Participants who take part in standard RCTs will make a judgment of their preferred treatment and often expect to be allocated to the treatment group [44]. If this does not occur, it can be followed by dissatisfaction and distrust in those who approached them to take part [45]. Consequently, randomization to a control group may lead to dropout after allocation. The original Zelen design involves randomization before consent, with consent only required from those allocated to the intervention, whereas the control group receive their usual care [24]. Baseline data and outcomes are collected from medical records (with ethical approval). However, it is not possible to have interaction with the control group during follow-up, as they are not informed of their presence in a study. Taking all of this into consideration, we hypothesized that women will accept the intervention because they perceive that it is needed for their support and protection. If they perceive it like this, they may not want to be randomized into control group or they may drop out after been randomized to usual care instead of intervention. To overcome this difficulty with acceptance of allocation to the control group, we followed the input of IPV survivors in a focus group we conducted [13]. Amongst other things the survivors informed us that they would prefer delayed intervention instead of usual care in a control group. The opinion of the participant representative in our project affirmed their support for this approach. A systematic review concluded that a delayed intervention could be an effective way of minimizing dropout [46]. In our pilot, thus we chose to offer to women of the control group a delay in the intervention. It is this specific challenge that is addressed in our pilot study. We wish to estimate the rates of acceptance of randomization primarily. We do not aim to estimate effect sizes. The approaches recommended for use of standardized effect sizes for pilot study sample sizes estimation are not applicable [47]. Our analytic approach will compute simple statistic with 95% CI and we will employ qualitative judgment in assessing the need to prepare a full-scale RCT.

Beyond the information described to be collected during this pilot, we will capture other relevant information in the cohort study useful for planning the future full-scale randomised control trial: number of women who were approached and agreed to fill in the IPV screening question, number of women where there was a study protocol violation, number of women exposed to physical IPV captured by the screening questions, number of pregnant women exposed to physical IPV that accept to participate in the intervention and in the control group, number of women willing to participate in follow-up interviews, the acceptability of the e-health package for ongoing IPV prevention and the acceptability of video-counselling for IPV prevention in terms of compliance [48] to the scheduled counselling sessions.

In conclusion, the pilot study nested within the cohort study will allow us to obtain information about the rates of IPV in pregnancy, the acceptability of an e-health intervention and the availability of participants for randomisation into an effectiveness trial. These results will inform us about the feasibility and variance of key clinical outcome measures for estimation sample size of the full-scale effectiveness trial.

